### Objectives

Hypotheses were as follows: (1) clear and appropriate information for the target population of the vaccination (middle school students aged 9 to 17 years) as well as for their parents will improve their knowledge about HPV vaccination and thus increase their adherence to this vaccination regimen, (2) combining information with vaccination in the school setting will improve coverage, as it will reduce any material obstacles that may prevent the vaccination process, and (3) raising awareness among general practitioners will enable them to better understand the benefits and risks of HPV vaccination and thus encourage families, who naturally trust them, to adhere to the program.

The main objective of the study is to evaluate, in a population of middle school girls on Reunion Island, the impact of a health promotion program on the proportion of middle school girls who complete the full HPV vaccination schedule (2 or 3 doses) by the end of school year.

The program, conducted during school year, will combine: (1) sexual health promotion (students and parents) during classes at school at the beginning of school year, (2) training of general practitioners (who practice in a perimeter of 5 km around the middle school) on HPV vaccination at the beginning of school year, and (3) free school-based vaccination (in a “health bus”) during the academic year.

Secondary objectives in the study population at the end of school year are as follows:

Assess the impact of the combined health promotion program on the proportion of middle school girls who initiated HPV vaccination (at least 1 dose)Assess the acceptability of the HPV vaccination program among middle school boysDescribe the barriers to HPV vaccination for both girls and boysAssess the acceptability of HPV vaccination in the school settingAssess the value of setting up a sexual health information point through a health busEvaluate the satisfaction of students, parents, and school workers with the measures put into placeEvaluate vaccination coverage for different mandatory vaccines according to the current national vaccination calendar

The aim of this study was to evaluate whether a health promotion program combining information and free school-based vaccination could raise HPV vaccination coverage.

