##### June: Data Collection in Randomly Selected Classes

At the end of school year (June), an investigator will collect data from health records at a specific time during class. In particular, the researcher will look for the presence of de novo HPV vaccination performed by general practitioners outside of the health bus. Signed consent of parents or holders of parental authority will be collected before any intervention in the study (ie, before data collection and before school vaccination is carried out).

Vaccination data, even if not collected at the time of the intervention, can be collected either during the vaccination campaigns, or during the intervention at the end of school year, especially for children whose parents have agreed to participate but not to be vaccinated in the health bus. Indeed, since vaccination dates appear in the health record, it will be possible afterward to know whether pupils were vaccinated before the interventions under study in order to have the vaccination rate at the very beginning of the study.

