### Statistical Analyses

#### Sample Size

To our knowledge, there are no recent studies that have evaluated the impact of school-based vaccination on HPV vaccination coverage rates. An experimental catch-up vaccination program (diphtheria, tetanus, poliomyelitis, pertussis, measles, mumps, rubella, meningococcus C, hepatitis B, and HPV) in schools in the Vosges (Eastern France) [18] showed a participation rate ranging from 42.9% in the first year to 29% in the second year.

The calculation of the study size is based on the expected proportion of vaccination among girls, as this is the main objective of this study and we have no data for vaccination among boys at this time. Statistical assumptions were as follow:

Proportion of schoolgirls who have had a complete HPV vaccination schedule at the end of school year of 6% in the control group for all students (compared to the 8.1% expected at age 16 years [12])Proportion of schoolgirls with a complete HPV vaccination schedule at the end of the school year of 20% in the intervention group

Thus, 87 girls in each group would need to be included to demonstrate this 14% difference at *α*=.05 and power (1−β=0.80). Assuming 15% nonanalyzable data (lost to follow-up, nonresponse), a total of 103 female students per group would need to be included. As there are roughly as many girls as boys in each class, we would need to include 206 students per group. In order to have an equal representation of each age group, the sampling will be stratified in the grades: 6th, 7th, 8th, and 9th grade. Thus, 52 students per grade and per group should be included.

If we consider that the classes contain an average of 22 students each, a minimum of 3 classes per grade should be randomly selected in each of the 2 middle schools to ensure the minimum necessary recruitment. Thus, randomly selecting 3 classes per grade in each of the 2 middle schools will make it possible to include approximately 132 female students per group and thus to ensure the minimum necessary recruitment. A total of 528 students are expected to be recruited (264 girls [132 per group] and 264 boys [132 per group]). The calculation of the number of subjects required was performed with PASS (version 15, NCSS) software.

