The analysis of barriers to vaccination will describe the causes of nonvaccination reported for students who did not initiate the vaccination schedule. Analyses will be performed for girls and boys separately. We will also compare sociodemographic data, medical history, and health care utilization data between students who initiated HPV vaccination at the end of the school year and those who did not in the intervention group. Bivariate comparisons of percentages will be performed by the chi-square test or Fisher exact test depending on validity conditions. For continuous variables, comparisons will be made using the Student *t* test or the Mann-Whitney *U* test, depending on the conditions of validity. A multivariate analysis by logistic regression will be carried out in order to take into account confounding phenomena: the variable to be explained will be the fact of having initiated vaccination at the end of the school year, and the explanatory variables entered in the model will be the variables for which the significance threshold in bivariate analysis will be ≤.20.

To be determined in the intervention group: among students who initiated HPV vaccination at the end of school year, the proportion of students who used the health bus to initiate this vaccination. Among students who completed the full vaccination schedule at the end of school year, we will determine the proportion who completed all injections on the health bus.

In the intervention group, the proportion of students who used the health bus for sexual health information will be evaluated. In the intervention group, positive and negative points reported by students, their parents, and school staff about this program will be described. Proportion of students up to date for each type of vaccine (according to current vaccination calendar) at the end of school year, in the entire study population as well as in each of the 2 groups (intervention and control), and comparison of these proportions between the 2 groups by the chi-square test or Fisher exact test will be determined, according to validity conditions.

Analyses comparing control group to intervention group will all be performed on an intention-to-treat basis. All hypotheses will be tested with bilateral tests and *α*=.05 and confidence interval calculated at 95%. Analyses will be performed using SAS (version 9.4, SAS Institute Inc) software.

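### The school-against-school test of non-HPV vaccine coverage ignores status before the program, so it carries over any prior gap and dilutes in-year catch-up (minor, secondary outcome)

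*Protocol article*

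**What the plan says.** Under Objectives, the last secondary objective is to evaluate "vaccination coverage for different mandatory vaccines according to the current national vaccination calendar". It is worded as coverage. The first secondary objective, on HPV initiation, is worded as impact.

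Under Statistical Methods for Primary and Secondary Outcomes, the outcome becomes "Proportion of students up to date for each type of vaccine (according to current vaccination calendar) at the end of school year", reported for the whole study population and for each group, followed by "comparison of these proportions between the 2 groups by the chi-square test or Fisher exact test will be determined, according to validity conditions". The same section states "All hypotheses will be tested with bilateral tests and" a .05 level, and places all intervention-control analyses on an intention-to-treat basis. It plans a comparability check at inclusion, but this test makes no use of that check.

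Three other places bear on the point:

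- **Study Setting:** there is one school per arm. The two were designated on ability to participate, location and bus parking, not randomized.
- **HPV Vaccination in the Health Bus:** the bus offers HPV vaccine only.
- **June data collection:** the article notes that "since vaccination dates appear in the health record, it will be possible afterward to know whether pupils were vaccinated before the interventions under study", so as to recover the vaccination rate at the start of the study.

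**The concern.** Being up to date is a cumulative status. Pupils are aged 9 to 17 and the program lasts one school year, so part of each year-end proportion reflects doses given before the program began. A plain comparison of the two proportions cannot separate that history from what happened during the year.

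Two errors follow for the non-HPV vaccines. If the schools differed beforehand, the test can be significant although the program changed nothing. If the program did prompt catch-up, the effect is diluted by pupils who were already up to date, and it can be cancelled if the intervention school started lower. The result would sit beside the HPV comparisons, with the same test and the same .05 level, and could easily be taken for a program result.

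**Working it through.** **The plan's own figures.** No sample size or power is given for this outcome. The only stated calculation is for the primary outcome, and it reproduces. With 6% vs 20%, two-sided .05, power 0.80 and unpooled variance:

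n = (1.960 + 0.842)² × (0.06×0.94 + 0.20×0.80) / 0.14² = 86.66, so 87 per group; 87/0.85 = 102.4, so 103.

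**Inputs for this point.** Sequence Generation plans 256 and 255 pupils; I use 255 per group. Results reports 245 and 259 selected. Prior coverage, prior gaps and catch-up rates are assumptions, because the article gives none for other vaccines. Pupils are treated as independent. Rejection probabilities come from exact binomial enumeration of the uncorrected chi-square test.

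**1. Prior gap, no program effect (control school 80%).** A normal-approximation check for a 5-point gap:

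- pooled SE = √(0.825×0.175×2/255) = 0.03365
- unpooled SE = √((0.85×0.15 + 0.80×0.20)/255) = 0.03358
- Φ((0.05 − 1.960×0.03365)/0.03358) = Φ(−0.475) = 0.32

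The exact results agree:

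| Prior gap | Chance of p<.05 |
|---|---|
| 0 points | 5% |
| 2 points | 9% |
| 3 points | 14% |
| 5 points | 32% |
| 10 points | 89% |

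With 245 vs 259 pupils, gaps of 3, 5 and 10 points give 14%, 31% and 89%. If 15% of records cannot be analyzed (255 × 0.85 ≈ 217 per group), the 5- and 10-point gaps give 28% and 84%.

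**2. Dilution, no prior gap.** Assume 80% up to date beforehand in both schools, and in-year catch-up of 30% vs 10% among the rest.

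- Year-end: 0.80 + 0.20×0.30 = 86% vs 0.80 + 0.20×0.10 = 82%. Power of the planned test: 23.5%.
- Pupils not up to date at the start: 0.20 × 255 = 51 per group. Power of 30% vs 10% in that subset: 73%.

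The gain depends on the assumptions:

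| Up to date before | Catch-up | Planned test | Subset test |
|---|---|---|---|
| 70% | 30% vs 10% | 35.5% (79% vs 73%) | 89% (77 per group) |
| 80% | 30% vs 10% | 23.5% (86% vs 82%) | 73% (51 per group) |
| 80% | 20% vs 10% | 9% (84% vs 82%) | 29% (51 per group) |
| 90% | 30% vs 10% | 13% (93% vs 91%) | 47% (26 per group) |

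**3. Masking.** With 245 vs 259 pupils (normal approximation) and the control school at 80%, a true 10-point gain has 88% power if the schools start level. If the intervention school starts 5 points lower, the year-end gap is 5 points and power falls to 31%. If it starts 10 points lower, the gap is nil and the rejection rate is 5%.

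**The case against.** The best defense is that the objective asks for coverage, not impact. Year-end status is the correct quantity for coverage, and the stated expectations in the Conclusions and Principal Findings concern HPV only. Nothing says that a difference in other vaccines would be credited to the program. This stands for the description. It does not rescue the test, which is a stated intervention-control hypothesis test that the objective does not request.

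A large prior gap is also not established. Both schools are in priority education zones, and the class draw was stratified by grade and SEGPA to make the groups similar. That makes a 2- or 3-point gap as arguable as a 10-point one, so the range belongs in the point and the 89% is its upper end. Sampling classes alike within schools does not, however, equalize two designated schools.

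A reader might infer more than the documents support:

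- **That most of the status predates the program.** This is an inference from age and program length, and is weaker for a vaccine falling due in these grades. The false-effect argument needs only a prior gap.
- **That the program could not have affected other vaccines, or only through the class session.** Parent calls, practitioner information and referral to the general practitioner for later HPV doses could also prompt catch-up. Read literally, each type of vaccine also includes HPV, which the bus supplies; the point is confined to the others.
- **That the dates are already in the database.** The article says they appear in the health record. Records are returned at once, and nothing shown confirms that dates of non-HPV doses were transcribed.
- **That the objective and the methods list different vaccines by intent.** Both refer to the current calendar, so the methods wording may be shorthand. It still needs aligning.

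**Conclusion.** The point holds in limited form. The planned test for non-HPV vaccines cannot distinguish a gap that existed before the program from a change during it. Under the stated assumptions, a prior gap of 2 to 5 points raises the false-positive rate from 5% to between 9% and 32%, and a 10-point gap raises it to 89%. Dilution costs power in every scenario examined, but the gain from counting in-year catch-up is modest when catch-up rates are close or few pupils are behind. All these figures ignore clustering.

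This is a minor point on a secondary outcome. The coverage description is sound, and the primary result is not touched.

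**What to change.** 1. Keep year-end coverage, overall and by school, as a description. This meets the objective. State that no program claim is made from it.
2. For any between-group comparison of non-HPV vaccines, use the recorded dates to fix each pupil's status on one common start-of-program date in both schools. Compare the proportion brought up to date by year end among pupils not up to date on that date or newly due after it.
3. If the dates of non-HPV doses were not transcribed, drop the test and report the comparison as descriptive only.
4. Align the vaccine list in the statistical methods with the mandatory vaccines named in the objective.

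If the dates are held, the cost is a change of wording and some derivation. The tested subset is smaller, about 51 per group at 80% prior coverage. The change removes the carried-over gap only: with one school per arm, in-year catch-up is still confounded with school, and clustering remains. Both limits should be stated with the result.

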### Ethical Considerations

The sponsor and investigators agree that this research will be conducted in accordance with the law no. 2012-300 of March 5, 2012, relating to research involving human persons; Good Clinical Practices (version 4 of November 9, 2016, and decision of November 24, 2006); and the Declaration of Helsinki [19]. The research is conducted in accordance with this protocol. Except in emergency situations requiring the implementation of specific therapeutic procedures, the investigators undertake to comply with the protocol in all respects, in particular with regard to the collection of consent and the notification and follow-up of serious adverse events.

This research has received the favorable opinion of the research ethics committee (Comité de Protection des personnes (CPP); ethics committee for the protection of individuals) of Ouest II of Angers (No. 20.05.14.35227; 2020/46) and the authorization of the Agence nationale de la sécurité du médicament (ANSM), the French equivalent of the US Food and Drug Administration. The University Hospital of Reunion Island, promotor of this research, has taken out a civil liability insurance policy with the hospital insurance company Société hospitalière d’assurance mutuelle (no. 158958) in accordance with the provisions of the public health code.

The data recorded during this research are subject to computerized processing at the University Hospital of Reunion Island, responsible for data processing in compliance with the law no. 78-17 of January 6, 1978, relating to data processing, files, and freedoms modified by the law 2004-801 of August 6, 2004 and modified by the law no. 2018-493 of June 20, 2018. This research falls within the framework of the reference methodology (RM-001) in application of the provisions of Article 54 paragraph 5 of the amended Act of January 6, 1978, relating to information, files, and freedoms. This change was approved by decision of January 5, 2006, updated on July 21, 2016. The University Hospital of Reunion Island, responsible for data processing, has signed a commitment to comply with this reference methodology. The research sponsor undertakes to carry out the research in compliance with the General Data Protection Regulation of April 27, 2016, implemented on May 25, 2018. This research is registered in the ANSM European Union Drug Regulating Authorities Clinical Trials Database [73-2020] and at ClinicalTrials.gov [NCT04459221]. Authors obtained consent to participate in the study from participants and their parents (or holders of parental authority). Written, informed consent to participate was obtained from all participants.

### Availability of Data and Materials

The following documents relating to the research are archived by the investigator in accordance with Good Clinical Practice for a period of 15 years following the end of the research (research involving drugs, medical devices, or in vitro diagnostic medical devices or research not involving a product mentioned in article L.5311-1 of the public health code): the protocol and any amendments to the protocol, observation notebooks (copies), the source files of participants who have signed a consent form, and all other documents and letters related to the research.

Original copies of signed informed consents from participants and authority holders will be archived for a period of 30 years following the end of the research. All of these documents are the responsibility of the investigator for the regulatory archiving period. No movement or destruction will be made without the sponsor’s approval. At the end of the regulatory retention period, the sponsor will be consulted for destruction. All data, documents, and reports are subject to audit or inspection.

Within 1 year of the completion or termination of the research, a final report will be prepared and signed by the sponsor and investigator. This report will be made available to the competent authority. The sponsor will transmit the results of the research to the CPP and, if necessary, to the ANSM in the form of a summary of the final report within 1 year of the end of the research. The data sets generated and analyzed during this study are available from the corresponding author on reasonable request.

## Results

This study was funded in September 2019. Recruitment began in October 2020 (Figure 3). Concerning vaccination, recruitment was completed by June 2021. Concerning evaluation of satisfaction of participants and evaluation of barriers to HPV vaccination, completion of recruitment was completed by December 2021.

In the intervention school, of 780 students, 245 were randomly selected in the 12 classes. In the control school, 259 students out of 834 were randomly selected. Analyses are still ongoing, though it seems that this health promotion program offering information to students, parents, and general practitioners and free school-based vaccination had a positive impact on the intervention school and drew many students into the health bus for HPV vaccination.

**Figure 3 figure3:**
[figure not shown]
Intervention screenshots.

## Discussion

### Principal Findings

In this study, we expect significantly higher HPV vaccination coverage (full vaccination or first dose) in the intervention school as compared to the control school, whether it be among girls or boys.

### Comparison With Prior Work

Previous studies have already shown the benefits of school-based educational sessions to improve adolescent knowledge and behavior regarding HPV prevention and increase the likelihood of the students to become vaccinated [20,21]. Education interventions represent a simple yet potentially effective strategy for increasing HPV vaccination, especially when targeting groups influential to the HPV vaccination behaviors of adolescents: parents [22], school staff [23], and health care professionals [24]. Indeed, knowledge was associated with recommendation intention and behavior.

### Strengths and Limitations

This protocol is submitted more than a year after recruitment began, since sanitary COVID-19 condition was in constant change and evolution and it was difficult to know whether we could continue the process of the trial. Amendments were made and submitted to the ethics committee, facing prohibition of meetings with more than 6 people. This protocol is the result of our constant adaptation to these different obstacles.

Having different exclusion criteria for participants in the intervention and control arms m ay introduce a selection bias by design. However, we wanted to include as many children as possible in the control group to have a representative sample of the population, and the groups may still be comparable. The sample size calculation has not taken into account correlation between participants in the same cluster. As such, the sample size is likely to be too small. However, one limit is the price of the vaccine, which limited our ability to include more students, with regard to the funds allocated.

On Reunion Island, specificities regarding economic and societal development are as follows: high rate of universal health insurance coverage where the high cost of HPV vaccine may be a barrier, mixed culture with religious faith incompatible with premarital sex and racist biopolitical mistrust of the West from which the vaccine comes from, and the particular weight of the antivaccine leagues which casted a negative halo around the subject [25]. Thus we expect a strong veto from parents.

